| Efficacy outcomes | 
Primary outcome:
 
Proportion of patients with functional independence (modified Rankin scale (mRS) <math>\leq 2</math>) at 3 months after randomization.
 
Secondary outcomes:
 
 
1. Proportion of patients with recurrent stroke (ischemic stroke and intracerebral hemorrhage) at 3 months and 12 months after randomization;
 
2. Proportion of patients with functional independence (mRS <math>\leq 2</math>) at 12 months after randomization;
 
3. Proportion of patients with no or minimal disability (mRS <math>\leq 1</math>) at 3 months and 12 months after randomization;
 
4. Change in National Institutes of Health Stroke Scale score at 3 months after randomization;
 
5. Proportion of composite cerebrovascular events (ischemic stroke, intracerebral hemorrhage, myocardial infarction, and vascular death) at 3 months and 12 months after randomization;
 
6. Difference of EuroQoL Group 5-Dimension score at 3 months and 12 months after randomization;
 
7. Change in Barthel Index score at 3 months and 12 months after randomization;
 
8. Difference in platelet counts and coagulation indicators (prothrombin time, and activated partial thromboplastin time) at 3 months after randomization.
 
 |

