135 cerebrovascular diseases, and have been widely used in treating ischemic stroke. The pharmacological studies  
136 proved that panax notoginseng saponin has a wide range of biological activities and can significantly reduce  
137 hematocrit and fibrinogen content in the blood to reduce the blood viscosity; Rgl, an important component of  
138 panax notoginseng saponins, can significantly inhibit platelet aggregation and stimulate a reduction of the  
139 hematocrit and fibrin content in the blood and effectively prevent thrombosis. Patients with ischemic stroke who  
140 were treated with XST in addition to conventional treatment showed significantly better recovery of  
141 neurological function and improvement of daily living ability than the control group.

142 This multicenter, randomized, double-blind, controlled clinical trial aims to provide more evidence on the use  
143 of medications for neuroprotection in patients with ischemic stroke to further investigate the efficacy and safety  
144 of XST.

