### 3.4 Exclusion Criteria

1. Hemorrhage; or other pathologic brain disorders such as vascular malformations, tumors, abscesses, encephalitis; or other common non-ischemic brain diseases (e.g., multiple sclerosis) confirmed by head computed tomography (CT)/magnetic resonance imaging (MRI);
2. Had contraindications to panax notoginseng saponins:
  - 1) Known allergy history;
  - 2) Known allergy to agents including aspirin, salicylates, or any other ingredients of medicine included in the study;
  - 3) With a medical history of asthma caused by salicylates or substances containing salicylic acid, or non-steroidal anti-inflammatory drugs;
  - 4) Active peptic ulcers;
  - 5) Severe hepatic insufficiency or renal insufficiency  
(alanine aminotransferase  $> 2 \times$  upper limit of normal, or aspartate aminotransferase  $> 2 \times$  upper limit of normal; creatinine  $> 1.5 \times$  upper limit of normal);
  - 6) Severe cardiac failure;
  - 7) With a prior medical history of coagulopathy or systemic hemorrhages;
  - 8) With a prior medical history of thrombocytopenia or neutropenia;
  - 9) With a prior medical history of drug-induced blood system diseases or abnormal hepatic function;
  - 10) Leukopenia ( $< 2 \times 10^9/L$ ) or thrombocytopenia ( $< 100 \times 10^9/L$ );
  - 11) Female in the gestation or lactation period.
3. With indications for anticoagulation (suspected cardioembolism, such as atrial fibrillation, prosthetic heart valve, and suspected endocarditis);
4. With a medical history of intracranial hemorrhage or cerebral amyloid angiopathy;
5. With a medical history of aneurysm (including intracranial aneurysm and peripheral aneurysm);
6. Confirmed or suspected acute coronary syndrome;
7. High-risk bradyarrhythmia like sick sinus syndrome with second- or third-degree atrioventricular conduction block, bradycardia-related syncope induced by not installing a cardiac pacemaker;
8. With a history of gastrointestinal hemorrhage within 3 months prior to randomization, or undergoing a major surgery within 30 days prior to randomization;
9. Expected to receive endovascular treatment or operative treatment in the next 3 months;

- 189 10. Required to terminate the trial drug due to other scheduled surgery or interventional treatments;
- 190 11. Patients had severe non-cardiovascular or cerebrovascular diseases with a life expectancy of less than 3
- 191 months;

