### 203 **4.2 Secondary Efficacy Outcomes**

- 204 1. Proportion of recurrent stroke (ischemic stroke and intracerebral hemorrhage) at 3 months and 12 months
- 205 after randomization;
- 206 2. Proportion of patients with functional independence ( $mRS \leq 2$ ) at 12 months after randomization;
- 207 3. Proportion of patients with no or minimal disability ( $mRS \leq 1$ ) at 3 months and 12 months after
- 208 randomization;
- 209 4. Change in NIHSS score at 3 months after randomization;
- 210 5. Proportion of composite cerebrovascular events (ischemic stroke, intracerebral hemorrhage, myocardial
- 211 infarction, and vascular death) at 3 months and 12 months after randomization;
- 212 6. Difference of EuroQoL Group 5-Dimension (EQ-5D) score at 3 months and 12 months after
- 213 randomization;
- 214 7. Change in Barthel Index (BI) score at 3 months and 12 months after randomization;
- 215 8. Difference of platelet counts and coagulation indicators (prothrombin time, and activated partial
- 216 thromboplastin time) at 3 months after randomization.

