### 219 **4.4 Secondary Safety Outcomes**

- 220 1. Incidence of symptomatic intracranial hemorrhage within 3 months of treatment;
- 221 2. Incidence of all-cause mortality within 3 months of treatment;
- 222 3. Incidence of AEs within 3 months of treatment.

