##### **13.2.2 Efficacy Analysis**

Primary endpoint: According to the basic principle of intention-to-treat analysis, Chi-square test or Fisher's exact test will be used for data in the modified intention-to-treat cohort to evaluate efficacy. In addition, a logistic regression model will be adopted to calculate the odds ratio (OR) between the two treatment regimens, with center effects set as random effects in the model.

Secondary endpoint: The primary endpoint analysis strategy will be used for most secondary endpoint analyses. Wilcoxon rank-sum test will be used for measurement data to analyze differences between the two groups. For survival data, the Kaplan-Meier method will be used to estimate the survival rate of each group and plot survival curves, log-rank test will be used for efficacy evaluation, and Cox proportional hazards model will be used to calculate the hazard ratio (HR) between the two treatment regimens. For non-survival data, Chi-square test or Fisher's exact test will be used, and a logistic regression model will be used to calculate the OR value. Center effects will be set as random effects in all the models.

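### Platelet count, PT and APTT are classed as efficacy with no direction of benefit, and the efficacy analysis suits them poorly as hazard markers

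*Protocol*

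**What the plan says.** The Summary of Protocol lists as secondary efficacy outcome 8: "Difference in platelet counts and coagulation indicators (prothrombin time, and activated partial thromboplastin time) at 3 months after randomization". Section 4.2 repeats the item under the same efficacy heading ("Difference of platelet counts and coagulation indicators (prothrombin time, and activated partial" thromboplastin time). Neither place gives a direction of benefit, a limit or a reference range.

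Section 4.3 (serious adverse events) and section 4.4 do not name these tests. The closest specific item in 4.4 is "Incidence of symptomatic intracranial hemorrhage within 3 months of treatment"; the others are all-cause mortality and adverse events overall.

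Section 3.4, under contraindications to the saponins, lists "With a prior medical history of coagulopathy or systemic hemorrhages", "With a prior medical history of thrombocytopenia or neutropenia", and a platelet count below 100 × 10⁹/L.

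On mechanism, section 1 says that a component of the saponins "can significantly inhibit platelet aggregation and stimulate a reduction of the" hematocrit and fibrin content of the blood. It does not say that a lower platelet count or a longer clotting time is a benefit.

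On analysis, section 13.2.2 states that "Wilcoxon rank-sum test will be used for measurement data to analyze differences between the two groups". Section 13 makes tests two-sided at 0.05. Section 13.1.1 makes the modified intention-to-treat (mITT) cohort primary for efficacy and fills missing values by last observation carried forward (LOCF).

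**The concern.** Under the protocol's own eligibility logic, a falling platelet count or impaired clotting is a hazard. Under its outcome list, a difference in the same tests is efficacy, with nothing to say whether a significant result in either direction is good or bad. A lower count or longer PT in the XST arm could therefore be presented as a pharmacological effect in its favour.

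The label also fixes the method. For a hazard marker one wants observed values in everyone dosed and a count of patients outside limits. The efficacy route instead carries old values forward and compares whole distributions by rank. Both features tend to hide a marked fall in a small number of patients.

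**Working it through.** **1. Sample size used as the basis.** Section 13.3 assumes 45% versus 50.4% (45% × 1.12), two-sided 0.05, power 0.80. With pooled variance under the null:

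n = [1.960·√(2 × 0.477 × 0.523) + 0.8416·√(0.504 × 0.496 + 0.45 × 0.55)]² / 0.054² = 1342 per arm.

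Allowing for 10% loss, 1342 / 0.90 = 1492. Both stated figures reproduce and are not in dispute. The protocol gives no power figure for outcome 8; 1342 per arm is used below as the number with data.

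**2. What LOCF does to these tests.** The section 6.1 schedule places laboratory tests at Day 1 and month 3 only, and section 6.1.1 makes Visit 1 the baseline. For a patient without a month-3 sample, the last scheduled value is therefore the pre-treatment one. Such patients can still be in the mITT cohort: section 7.6.3 allows follow-up by telephone after stopping the drug, which can supply an mRS but not a blood sample. They are then analysed as unchanged, which biases towards no harm.

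**3. Rank-sum power for a general shift.** Using the normal approximation with relative efficiency 3/π, power = Φ(d·√(n·(3/π)/2) − 1.96). With n = 1342 the multiplier of d is √(1342 × 0.955/2) = 25.3.

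- d = 0.10 SD: Φ(2.53 − 1.96) = 0.72
- d = 0.15 SD: Φ(3.80 − 1.96) = 0.97
- d = 0.20 SD: above 0.99

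**4. Rank-sum power for a severe fall in a few patients.** If a fraction f of the XST arm drops to the bottom of the distribution and the rest are unchanged, P(XST < control) moves by f/2. Its standard error is √((2n+1)/(12n²)) = √(2685/(12 × 1342²)) = 0.01115. For f = 1% (about 13 patients), z = 0.005/0.01115 = 0.45 and two-sided power is 0.073.

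Simulation (1000 runs, 1342 per arm) agrees. The third column assumes that half of the affected patients lack the month-3 sample and are given their baseline value. The fourth is Fisher's test on the proportion below a limit, assuming a 0.2% background.

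| Affected fraction of XST arm (assumed) | Rank-sum | Rank-sum, half of affected filled by LOCF | Proportion below limit |
|---|---|---|---|
| 0.5% | 0.06 | 0.06 | 0.38 |
| 1% | 0.08 | 0.06 | 0.87 |
| 2% | 0.15 | 0.07 | about 1.0 |
| 3% | 0.27 | 0.11 | about 1.0 |
| 5% | 0.60 | 0.19 | about 1.0 |
| 7% | 0.88 | 0.33 | about 1.0 |

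The last column depends on the background rate. At 0.5% versus 1.5% the power is about 0.70 by Fisher simulation, or 0.74 by normal approximation. The affected fractions, the background rates and the half-missing share are assumptions; the protocol gives none of them.

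**The case against.** A reader might infer that harm would be reported as efficacy, by a test that cannot see it. The protocol does not support either half of that.

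First, there is a safety route. Section 10.1 counts abnormal laboratory results as adverse events, section 10.2 has them recorded in every patient given at least one dose, and section 13.2.3 tabulates adverse events by arm. Adverse-event incidence is itself a secondary safety outcome, and section 8.4.1 has the DSMB reviewing safety data regularly. A patient with marked thrombocytopenia belongs in those tables whatever label outcome 8 carries. This stands, with a limit: the protocol sets no value at which a platelet count, PT or APTT counts as abnormal. Section 13.2.3 also leaves its items of interest unnamed, so no comparison of these tests is assured.

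Second, the rank-sum test is two-sided and sensitive to a general shift in either direction, as step 3 shows. Its weakness is confined to a rare, severe tail and to values replaced by LOCF. This stands in full.

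Third, the contraindications show who is kept out, not that the drug is expected to lower platelets. Markers of clotting are also a defensible exploratory choice for a drug with a claimed antithrombotic action. That is fair, but such a choice still needs a stated direction, and the background speaks of aggregation rather than count.

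Fourth, on observed month-3 values the mITT and safety cohorts nearly coincide, because bloods and efficacy scales are taken at the same visit. That also stands: most of the gain comes from dropping LOCF, not from changing the cohort.

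Finally, the statistical analysis plan is not shown and may add limits or tables. It would not alter the efficacy classification, which the protocol fixes.

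**Conclusion.** The point holds in a limited form. Three laboratory measures that the protocol elsewhere treats as markers of hazard are classed as efficacy with no direction. The efficacy analysis then fills gaps with pre-treatment values and relies on a test with little power against a severe fall in a few patients: about 7–8% if 1% are affected, and 27% if 3% are affected. For a general shift the planned test is adequate.

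A difference could be read as efficacy. That it would be, or that harm would go unrecorded, is not supported, because the adverse-event route exists. The contrast between 7–8% and about 87% power at 1% affected illustrates one assumed scenario and does not measure a defect in the plan. The primary outcome and the sample size are untouched. This is an inexpensive improvement worth making.

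**What to change.** - Move outcome 8 from section 4.2 to section 4.4, and make the same change in the Summary of Protocol.
- Analyse observed month-3 values in the safety cohort without LOCF, and report by arm how many patients lack a month-3 result.
- State that a falling platelet count or a prolonged PT or APTT is the direction of harm.
- Beside the existing rank-sum or median comparison, add by-arm counts of patients newly outside prespecified limits. Examples are platelets below 100 × 10⁹/L and PT or APTT above the local upper limit. The platelet figure is the protocol's own eligibility cut-off and would serve here only as an analysis limit, with no bearing on patient management.

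The cost is one fewer nominal efficacy outcome and one extra table, from data already collected. No visit or sample is added.

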**Abbreviations or Terminology**

| Abbreviations or Terminology | Description                                                                      |
|-------------------------------------|-----------------------------------------------------------------------------------------|
| AE                                  | Adverse Event                                                                           |
| BI                                  | Barthel Index                                                                           |
| CFDA                                | China Food and Drug Administration (now National Medical Products Administration, NMPA) |
| CRA                                 | Clinical Research Associate                                                             |
| CRF                                 | Case Report Form                                                                        |
| CT                                  | Computed Tomography                                                                     |
| DSMB                                | Data and Safety Monitoring Board                                                        |
| ECG                                 | Electrocardiograph                                                                      |
| EQ-5D                               | EuroQoL Group 5-Dimension                                                               |
| GCP                                 | Good Clinical Practice                                                                  |
| HR                                  | Hazard Ratio                                                                            |
| ICF                                 | Informed Consent Form                                                                   |
| IMP                                 | Investigational Medicinal Product                                                       |
| MRI                                 | Magnetic Resonance Imaging                                                              |
| mRS                                 | modified Rankin Scale                                                                   |
| NIHSS                               | National Institutes of Health Stroke Scale                                              |
| OR                                  | Odds Ratio                                                                              |
| PTDV                                | Premature Treatment Discontinuation Visit                                               |
| QC                                  | Quality Control                                                                         |
| SAE                                 | Serious Adverse Event                                                                   |

## 111 1. Background

112 Stroke is characterized by high morbidity, disability, and mortality, and has become one of the major threats to  
113 human health. The Global Burden of Disease Study showed that ischemic heart disease and stroke were the top  
114 causes of death globally between 1990 and 2010. Meanwhile, the burden of disease study in China showed that  
115 stroke was the leading cause of deaths among the Chinese in 2010, accounting for 29.4% of stroke-caused  
116 deaths worldwide. Ischemic stroke accounts for approximately 70% of all strokes. However, there is a lack of  
117 effective neuroprotective agents for ischemic stroke. Therefore, the development of a scientific and inexpensive  
118 neuroprotective agent with few adverse effects has become a research hotspot in the treatment of ischemic  
119 stroke.

120 Currently, the Chinese economy has entered a new era of development, with the status and role of the  
121 traditional Chinese medicine in the economic and social development gaining increasing importance. The  
122 revitalization and development of the traditional Chinese medicine are about to embrace a historic opportunity  
123 with favorable international and domestic environment while receiving popular support. In recent years, scholars  
124 have recommended the use of traditional Chinese medicine more often in the prevention and treatment of  
125 cardiovascular and cerebrovascular diseases.

126 Xuesaitong soft capsules (XST; trade name: LI XU WANG®) are prepared from an active ingredient - panax  
127 notoginseng saponins from the famous and precious medical herb - panax notoginseng. It was formally launched  
128 in the market in June 1999 after obtaining a new drug certificate and production approval issued by the China  
129 Food and Drug Administration (CFDA, now National Medical Products Administration, NMPA). After more  
130 than 10 years of development, production and clinical application, the safety of this product is proved to be good  
131 with low incidence of adverse events (AEs). The statistics of the National Adverse Drug Reaction Monitoring  
132 System in China showed that, from 2011 to May 2017, a total of 119 cases of AEs were reported, mostly  
133 gastrointestinal reactions, dizziness, headache, rash, anaphylactoid reactions, palpitations, and nausea. Ever  
134 since it has been marketed, XST have displayed significant protective effects in cardiovascular and  
135 cerebrovascular diseases, and have been widely used in treating ischemic stroke. The pharmacological studies  
136 proved that panax notoginseng saponin has a wide range of biological activities and can significantly reduce  
137 hematocrit and fibrinogen content in the blood to reduce the blood viscosity; Rgl, an important component of  
138 panax notoginseng saponins, can significantly inhibit platelet aggregation and stimulate a reduction of the  
139 hematocrit and fibrin content in the blood and effectively prevent thrombosis. Patients with ischemic stroke who  
140 were treated with XST in addition to conventional treatment showed significantly better recovery of  
141 neurological function and improvement of daily living ability than the control group.

142 This multicenter, randomized, double-blind, controlled clinical trial aims to provide more evidence on the use  
143 of medications for neuroprotection in patients with ischemic stroke to further investigate the efficacy and safety  
144 of XST.

## 145 2. Hypothesis

146 For patients with ischemic stroke within 14 days of onset, XST can further improve the 90-day functional  
147 outcome.

## 148 3. Patients

### 149 3.1 Sample Size

150 A total of 3000 eligible patients will be enrolled.

### 151 3.2 Diagnostic Criteria

The diagnostic criteria for ischemic stroke are shown in Appendix 1 in detail.

### 3.3 Inclusion Criteria

1. Aged 18-75 years;
2. Clinical diagnosis of ischemic stroke within 14 days of symptom onset;
3. Pre-stroke modified Rankin Scale (mRS)  $\leq 1$ ;
4.  $4 \leq$  National Institutes of Health Stroke Scale (NIHSS) score  $\leq 15$ ;
5. Signed written informed consent.

### 3.4 Exclusion Criteria

1. Hemorrhage; or other pathologic brain disorders such as vascular malformations, tumors, abscesses, encephalitis; or other common non-ischemic brain diseases (e.g., multiple sclerosis) confirmed by head computed tomography (CT)/magnetic resonance imaging (MRI);
2. Had contraindications to panax notoginseng saponins:
  - 1) Known allergy history;
  - 2) Known allergy to agents including aspirin, salicylates, or any other ingredients of medicine included in the study;
  - 3) With a medical history of asthma caused by salicylates or substances containing salicylic acid, or non-steroidal anti-inflammatory drugs;
  - 4) Active peptic ulcers;
  - 5) Severe hepatic insufficiency or renal insufficiency  
(alanine aminotransferase  $> 2 \times$  upper limit of normal, or aspartate aminotransferase  $> 2 \times$  upper limit of normal; creatinine  $> 1.5 \times$  upper limit of normal);
  - 6) Severe cardiac failure;
  - 7) With a prior medical history of coagulopathy or systemic hemorrhages;
  - 8) With a prior medical history of thrombocytopenia or neutropenia;
  - 9) With a prior medical history of drug-induced blood system diseases or abnormal hepatic function;
  - 10) Leukopenia ( $< 2 \times 10^9/L$ ) or thrombocytopenia ( $< 100 \times 10^9/L$ );
  - 11) Female in the gestation or lactation period.
3. With indications for anticoagulation (suspected cardioembolism, such as atrial fibrillation, prosthetic heart valve, and suspected endocarditis);
4. With a medical history of intracranial hemorrhage or cerebral amyloid angiopathy;
5. With a medical history of aneurysm (including intracranial aneurysm and peripheral aneurysm);
6. Confirmed or suspected acute coronary syndrome;
7. High-risk bradyarrhythmia like sick sinus syndrome with second- or third-degree atrioventricular conduction block, bradycardia-related syncope induced by not installing a cardiac pacemaker;
8. With a history of gastrointestinal hemorrhage within 3 months prior to randomization, or undergoing a major surgery within 30 days prior to randomization;
9. Expected to receive endovascular treatment or operative treatment in the next 3 months;

- 189 10. Required to terminate the trial drug due to other scheduled surgery or interventional treatments;
- 190 11. Patients had severe non-cardiovascular or cerebrovascular diseases with a life expectancy of less than 3
- 191 months;
- 192 12. Women of childbearing age showing negative pregnancy test but refusing to take effective contraceptive
- 193 measures;
- 194 13. Currently receiving an investigational drug or being involved in a device experiment;
- 195 14. Participated in other drug clinical trials and received other Investigational Medicinal Products (IMPs)
- 196 within 30 days before randomization;
- 197 15. Unable to understand and/or comply with the study procedures and/or follow-up due to psychiatric
- 198 disorders, cognitive, or mental disorders;
- 199 16. Patients are not eligible for this clinical trial as evaluated by the investigator.

